#### Mass Spectral Analysis of Glucose, Fructose, and Related Metabolites

Human serum or plasma samples will be thawed on an ice bath to minimize sample degradation. Metabolites will be extracted by adding 0.5 mL of 50% methanol (–20 °C) followed by homogenization for 3 minutes using a Bullet Blender Tissue Homogenizer (Next Advance, Inc) and centrifugation at 13,500 g for 10 minutes at 4 °C. The resulting 50 μL of supernatant will be transferred to a 1.5 mL tube and mixed with 10 μL of 200 mM 3-nitrophenylhydrazine (3-NPH) solution and 10 μL of mixed 96 mM ethylene dichloride/pyridine methanolic solution. Derivatization will be conducted by incubation at 30 °C for 1 hour before evaporation to dryness under nitrogen. 400 μL of 50% aqueous methanol will be used to resuspend the samples. The supernatants will be used for ultra-performance liquid chromatography coupled with quadrupole/time-of-flight mass spectrometry (UPLC-QTOF-MS) analysis according to previous reports with minor modifications [42,43].

#### Metabolomics-Related Measurement of Depression

##### Metabolomics Analysis

Ultra-performance liquid chromatography triple quadrupole mass spectrometry (UPLC-TQ-MS) (Xevo TQ-S system, Waters Corp) will be used to quantitatively measure the metabolites (neurotransmitters) selected as potential markers of depression. Briefly, an aliquot of 40 μl of urine or plasma will be spiked with 10 μL of internal standard (L-4-chlorophenylalanine in water, 30 μg/mL) and extracted with 200 μL of acetonitrile and methanol (9:1, v/v). The mixture will be vortexed and centrifuged. After centrifugation, the supernatant will be transferred to the sampling vials and subject to UPLC-TQ-MS analysis. The raw data generated will be processed using the TargetLynx Applications Manager Version 4.1 (Waters Corp) for targeted metabolite annotation and to obtain the calibration equations and the concentration of each metabolite in the samples.

##### Quality Control

Reproducible and valid results are critical for biomarker development. To achieve this, three types of quality control (QC) samples will be used in our metabolomics analysis: internal standards, test mixtures, and pooled biological samples. In addition to these QC samples, conditioning and solvent blank samples are required to obtain optimal instrument performance. Test mixtures comprise a group of commercially available standards with a mass range across the system mass range used for the study samples. These samples are analyzed at the beginning and end of each batch run to ensure that the instruments are performing within analytical specifications, such as retention time stability, peak resolution, peak signal intensity, and mass accuracy. Internal standards will be added to the test samples to monitor analytical variations during the entire sample preparation and analysis processes. The quality assurance criteria used to monitor the internal standards include (1) coefficient of variation (CV) ≤15% within 100 injections; (2) CV ≤20% within 300 injections. The CV is defined as the ratio of the standard deviation to the mean peak signal intensity. A pooled plasma sample containing aliquots from representative participants will be used as a study QC sample for the correction of interbatch analysis. The QC samples for this project will be prepared with the test samples and injected at regular intervals, every 12 testing samples, throughout each analytical run. The purpose of using the pooled QC samples is to provide a set of data that can be used to assess overall reproducibility and to correct for potential analytical variations. To minimize the batch-to-batch and day-to-day variations, we will attempt to arrange one case and one control sample adjacent to each other in each batch and on each day of testing. (3) Data assembly: for data analysis, the quantitatively measured metabolites for each participant will be merged with the participant’s clinical information through their individual sample IDs.

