### Blinding

One copy of the blind codes will be held by the project-responsible unit. The investigator operating the allocation of patients will not be involved in the intervention delivery, outcome measurements, or data analysis. The results of the allocation (being in the intervention or control groups) will be concealed from patients due to the waiting list control design, where patients in the control group will also receive a type of intervention and therefore will not know they are control participants. In addition, investigators assessing effects and those analyzing the data will also be blinded from the allocation.

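### The metabolomics batch layout is written for a case-control study and does not fit four randomised arms sampled at three visits and compared on change

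*Protocol article*

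**What the plan says.** The rule is in the Quality Control section, under Metabolomics-Related Measurement of Depression. Its stated purpose is "To minimize the batch-to-batch and day-to-day variations", and the means is that the laboratory will attempt to "arrange one case and one control sample adjacent to each other in each batch", and likewise on each testing day. The section does not define *case* or *control*, and it does not say how the arms or a patient's visits are spread over batches.

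The same section plans other safeguards. A pooled plasma sample "will be used as a study QC sample for the correction of interbatch analysis"; it is "injected at regular intervals, every 12 testing samples, throughout each analytical run", and serves "to assess overall reproducibility and to correct for potential analytical variations". Internal standards go into the test samples, and test mixtures are run at the beginning and end of each batch.

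The design that the rule has to serve is set out elsewhere in the article:
- Randomization and Allocation Concealment: four groups of equal size.
- Waiting List Control: one of the four is untreated during the study.
- Outcomes and Blood Biochemistry: measurement at baseline, week 13 and week 25, with three blood draws.
- Statistical Analysis: a mixed model comparing groups on change.
- Sample Size Calculation: 172 patients, 43 per group.

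**The concern.** Placing a case beside a control makes a batch shift common to both members of the pair, so it drops out of their difference. That works in a study with two groups of equal size and one sample per person. This trial differs in three ways.

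1. There are three active arms for one untreated arm, so one-to-one pairing runs out of controls.
2. The objectives in the Introduction hypothesise that the combination does better than the single treatments, including in modulating microbiome-related metabolites. Active arms must therefore be compared with each other, and pairing each with the waiting list does not balance them across batches.
3. The outcome is change within a patient. An additive batch shift cancels from change only if the patient's samples share a batch, and the rule does not ask for that.

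At stake are the precision of change in the metabolite outcomes and, where arms end up unevenly spread over batches, the validity of the arm contrasts. Once the samples have been run, a poor layout cannot be redone.

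**Working it through.** **The plan's own figure.** Two means, d = 0.8, two-sided alpha 0.05, power 90%, by t-test: 33.8, so 34 per group. Allowing for 20% drop-out, 34 / 0.8 = 42.5, so 43 per group and 4 × 43 = 172. The stated sample size is reproduced. It is used below only to count samples.

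**Coverage of the pairing rule** (per specimen type, full follow-up, active arm = case, waiting list = control, each control used once):
- all samples: 172 × 3 = 516
- waiting list: 43 × 3 = 129
- active arms: 129 × 3 = 387
- in pairs, at most: 129 + 129 = 258
- active-arm samples without a partner: 387 − 129 = 258, which is 67% of active-arm samples and 50% of all samples

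The other possible reading, case = depressed participant, does not help. The section on self-reported measures uses only the anxiety and stress subscales of the depression-anxiety-stress scale, the article gives no definition of a depression case, and such pairing would not balance arms.

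**Precision of change.** Let b be the residual batch SD after QC correction, in units of the outcome SD, and ρ the within-patient correlation. Both are assumptions, since the article gives neither.
- visits in the same batch: Var(change) = 2(1 − ρ)
- visits in different batches: Var(change) = 2(1 − ρ) + 2b²
- SD ratio = √{[2(1 − ρ) + 2b²] / [2(1 − ρ)]}

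| b | ρ = 0.5 | ρ = 0.7 |
|---|---|---|
| 0.1 | √(1.02/1.00) = 1.01 | √(0.62/0.60) = 1.02 |
| 0.3 | √(1.18/1.00) = 1.09 | √(0.78/0.60) = 1.14 |
| 0.5 | √(1.50/1.00) = 1.22 | √(1.10/0.60) = 1.35 |

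**Arm contrast.** Simulation with no treatment effect: two arms of 43, two visits, ρ = 0.5, four batches per visit, a patient's two visits in different batches, change compared without a batch term, 3000 runs per setting. Type I error at nominal 5%:

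| Layout | b = 0.1 | b = 0.3 | b = 0.5 |
|---|---|---|---|
| arms matched within batch | 5.4% | 3.8% | 2.9% |
| each arm in its own batches | 7.4% | 20% | 35% |

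Matching arms within batch protects the contrast. Values below 5% arise because the common shift stays in the error variance when batch is not modelled. Complete separation of arms is a worst case that the plan does not propose. It shows what balance is worth, and the pairing rule gives no such balance between the three active arms.

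**The case against.** The strongest reply is that the sentence is a best-effort aim in a condensed article, next to a proper QC scheme. Much of this stands, and it rules out several stronger readings that a reader might infer.

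- *The rule cannot be carried out.* The text says the laboratory will attempt it, and pairs can be formed within a visit. Only complete coverage is impossible.
- *The rule puts batch shift into every patient's change.* The article leaves open whether a patient's visits are split, and the pooled QC sample is there to correct interbatch shift. Only a residual can remain, and only if visits are split.
- *Pairing creates false arm differences.* Where arms are matched within batch, type I error is not inflated.
- *516 samples exceed a run limit.* The criterion "CV ≤20% within 300 injections" is an acceptance limit for the internal standards. It does not cap the length of a run.
- *The variance of change rises by 25% to 56%.* One could get this from an assumed within-patient CV of 20% and batch CVs of 10% and 15%: (0.04 + 0.01)/0.04 = 1.25 and (0.04 + 0.0225)/0.04 = 1.56. The batch CVs are assumed and uncorrected, and the plan's CV limits describe internal-standard peak intensity, which is a different quantity.
- *Layout by arm breaks the blind.* The Blinding section says that "investigators assessing effects and those analyzing the data will also be blinded from the allocation". Allocation is held as coded identification numbers, so a run list can be prepared from codes without unblinding the laboratory or the analysts.

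The reply does not rescue the rule itself. This is a stated instruction, so brevity does not explain it, and it names two groups where the trial has four. The plan also treats QC correction as not sufficient alone, since it adds a layout rule for the same purpose.

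**Conclusion.** The point holds as a mismatch between a stated rule and the design. The layout should be restated for four arms and three visits. Under the active-versus-waiting-list reading it reaches at most half of the samples (258 of 516), leaves the active arms unbalanced against each other, and does not keep visits together.

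The harm depends on a residual batch shift that the article does not quantify. Over the assumed range it goes from negligible (a 1% rise in the SD of change) to material (35%) if visits are split. Bias arises only to the extent that arms are unevenly spread over batches. The documents do not show that either will happen; the rule simply does not guard against them.

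The scope is the metabolomics outcomes, mainly the neurotransmitter panel under whose heading the rule stands. The mediators named in Statistical Analysis are the gut microbiome and immune function tests, not this panel. The sample size of 172 and the other outcomes are unaffected. The change is still worth making because it is cheap beforehand and impossible after the assays.

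**What to change.** Replace the case-control sentence in Quality Control with a layout rule for this trial:

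1. Run all available samples of a patient (up to three) in the same batch, in random order.
2. Balance the four arms within each batch, using coded labels and a run list prepared by the independent statistician who generates the allocation sequence.
3. Include batch in the metabolite model, for example as a random effect.
4. Keep the pooled-QC correction, internal standards and test mixtures as planned.

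The rule fits the existing QC spacing. One patient from each arm with three visits gives 4 × 3 = 12 samples, which is the planned interval between pooled QC injections. At full follow-up, 172 / 4 = 43 such sets make up the 516 samples.

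The cost is a run list, a set of coded labels, and samples kept frozen until the patient's week-25 sample is in. Storage at −80 °C is already planned for serum in Blood Biochemistry. Baseline samples will be stored longer than week-25 samples, but equally so in all arms, so the arm contrast is not affected by this.

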#### QoL and Other Mental Health-Related Measures (Self-Reported)

QoL will be measured using the Personal Well-being Index-Chinese Version. It is a subjective QoL measure that has been translated and validated. Anxiety will be measured using the Chinese version of the Depression Anxiety Stress Scale-21, which has been proven to have internal consistency [44,45]. The scale will discriminate between the negative emotional syndromes of depression, anxiety, and stress in Chinese populations. Only the subscales of anxiety and stress will be used. Loneliness will be measured using the Revised UCLA Loneliness Scale) [46,47]. This scale consists of 20 items and has been widely used to assess loneliness in research. General mental health will be measured using the General Health Questionnaire, which is commonly used to screen minor psychiatric symptoms [48].

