In addition to exercise intervention strategies, Chinese herbal medicines targeting gut microbiome dysbiosis have also been reported to improve immune function [11], facilitating patients’ recovery. The gut microbiome influences immune function and immune homeostasis both within the gut and systematically [12]. Chinese herbal medicines, the gut microbiome, and microbial metabolites regulate immune function and intestinal permeability involved in the pathological processes of virus-induced autoimmune diseases [11]. Restoring gut microbiome composition and its regulatory metabolites could be vital in boosting immune function and aiding recovery from COVID-19. Additionally, patients with COVID-19 experience loneliness, anxiety, depression, and decreased quality of life [13]. In summary, evidence suggests that exercise or Chinese medicines can help patients recover from virus-induced immune diseases and respiratory conditions such as pulmonary fibrosis. However, the potential beneficial individual and combined effects need further investigation.

In our proposed study, we will develop a new paradigm for the patient rehabilitation that is needed now and in the future. The specific aims of this project are (1) to investigate the effects of a 12-week programme involving cardiorespiratory exercise and Chinese herbal medicine, both singly and combined, on patients recovering from COVID-19 who exhibit pulmonary impairment and (2) to collect qualitative and quantitative data to examine the patients’ loneliness, anxiety, depression, quality of life, and mental health. A further aim will be to examine how Chinese herbal medicines as well as the gut microbiome and its metabolites regulate immune function, intestinal permeability, and possibly autoimmune deficiency in the pathological recovery and rehabilitation process. The specified study objectives and hypotheses are listed below:

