Evaluate the effects of cardiorespiratory exercise and Chinese herbal medicine, both individually and in a combination, on rehabilitation on pulmonary function among patients with COVID-19 through four intervention groups, including a cardiorespiratory exercise plus Chinese herbal medicines group, a cardiorespiratory exercise group in isolation, a Chinese herbal medicines group, and a waiting list control group (primary outcome). We hypothesize that the combination of cardiorespiratory exercise and Chinese herbal medicines will more greatly facilitate the rehabilitation of patients with COVID-19.Reveal whether and how the gut microbiome plays a role in the effects of cardiorespiratory exercise and Chinese herbal medicines, both individually and in combination, on the rehabilitation of impaired pulmonary function. We hypothesize that the combination of cardiorespiratory exercise and Chinese herbal medicines will better modulate the gut microbiome and the related metabolites and thus better mediate the effects.Assess the effects of cardiorespiratory exercise and Chinese herbal medicines on immune functions, both individually and in combination, on the rehabilitation of other relevant symptoms and signs of COVID-19. We hypothesize that the combination of cardiorespiratory exercise and Chinese herbal medicines will better modulate the immune function and thus better mediate the effects.Evaluate the effects of cardiorespiratory exercise and Chinese herbal medicines, both individually and in combination, on recovery from mental health-related outcomes (loneliness, stress, anxiety, depression) and on quality of life (QoL). We hypothesize that the combination of cardiorespiratory exercise and Chinese herbal medicines will better help postdischarge patients in recovery from mental health-related outcomes and improve their QoL.Assess the lasting effects of cardiorespiratory exercise and Chinese herbal medicines after a 12-week follow-up period. We hypothesize that some effects (eg, dyspnea, mental health-related outcomes, QoL) will be sustainable, while others (outcomes sensitively responded to cardiorespiratory exercise, eg, physical fitness, lung function) will partially relapse after the intervention cessation.

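### Depression is a named aim and objective, but the plan leaves out the DASS-21 depression subscale and names no other depression score

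*Protocol article*

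**What the plan says.** The second aim in the Introduction is "to collect qualitative and quantitative data to examine the patients’ loneliness, anxiety, depression, quality of life, and mental health". The fourth of the five listed objectives concerns "recovery from mental health-related outcomes (loneliness, stress, anxiety, depression) and on quality of life (QoL", and its hypothesis is that the combined treatment "will better help postdischarge patients in recovery from mental health-related outcomes and improve their QoL".

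Under QoL and Other Mental Health-Related Measures (Self-Reported), the DASS-21 is introduced for anxiety. The article then says of it: "The scale will discriminate between the negative emotional syndromes of depression, anxiety, and stress in Chinese populations". The next sentence restricts its use: "Only the subscales of anxiety and stress will be used". The other scales in that section are the Personal Well-being Index (quality of life), the Revised UCLA Loneliness Scale and the General Health Questionnaire (general mental health).

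Depression appears again as a laboratory measure. Under Metabolomics Analysis, mass spectrometry is to "quantitatively measure the metabolites (neurotransmitters) selected as potential markers of depression".

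**The concern.** The objective and the measurement section disagree. The objective promises a between-group assessment of depression. The measurement section picks an instrument that yields a depression score and then sets that score aside.

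At stake is what the trial could report on depression at the end. A result would have to come from a non-specific distress score or from candidate biomarkers. Neither is a depression rating, and a reader of the results could fairly ask what the depression claim was based on. A later analysis plan cannot easily repair this, because it cannot analyse a score that the protocol says will not be used.

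**Working it through.** The point carries no figure of its own, so the check is to match each construct in the fourth objective to a named self-report measure.

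| Construct in the fourth objective | Named self-report score |
|---|---|
| Loneliness | Revised UCLA Loneliness Scale |
| Stress | DASS-21 stress subscale |
| Anxiety | DASS-21 anxiety subscale |
| Depression | none |

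Three of four are covered and one is not.

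Next, could anything else in the article serve as the depression outcome?

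- **General Health Questionnaire.** It is assigned to general mental health and described as a screen for minor psychiatric symptoms. No version or subscale is given, so depression-specific content can be neither assumed nor ruled out.
- **Personal Well-being Index.** It is assigned to subjective quality of life.
- **Neurotransmitter metabolites.** Table 2 has a row for them and the article calls them potential markers. A candidate marker cannot stand in for the condition it may mark. The Quality Control section merges the metabolites with each participant's clinical information, but no depression rating is named in that information.
- **BDNF and corticosterone.** Blood Biochemistry introduces these as markers related to emotional disturbance. They are not depression ratings.
- **Qualitative data and the open-ended Table 2.** The second aim mentions qualitative data, and the Outcomes section says the table is not exhaustive. Neither names a depression score, and an open-ended list does not override a stated restriction.

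Then timing. The Outcomes section schedules all measurements at baseline and at weeks 13 and 25. The Statistical Analysis section compares changes between groups, so a depression analysis on the same lines needs a baseline score as well as later ones.

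Last, does the sample size depend on this? From Sample Size Calculation: effect size 0.8, significance level 0.05 (two-tailed, per Statistical Analysis), power 90%, dropout 20%. A two-sample t-test gives 33.83, so 34 per group. Then 34 / (1 − 0.20) = 42.5, so 43 per group, and 4 × 43 = 172, which is the stated figure. The effect size comes from a meta-analysis of dyspnea and exercise capacity. Depression does not enter, and 172 stands whichever way the contradiction is resolved.

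**The case against.** The strongest reply is that the plan is not empty on depression. Table 2 lists a metabolomic measurement under that name, the General Health Questionnaire gives a distress score, and qualitative data are promised. This has force against three stronger conclusions that a reader might draw.

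- **That no depression outcome exists at any visit.** The documents do not support this. A depression-labelled laboratory measure is listed and scheduled. What is missing is a depression-specific clinical score.
- **That the depression metabolomics cannot be interpreted.** This does not follow. Metabolite concentrations can be compared between groups over time with the planned mixed model, and related to the anxiety, stress and General Health Questionnaire scores. The article states no analysis that validates them against a depression rating. The missing score limits what they can say about depression specifically.
- **That the baseline depression score is lost for all 172 patients.** The article says which subscales will be used, not which items will be given. If the whole form is administered and the depression items are simply left unscored, the baseline can be recovered. The 172 is also a preliminary target that the article says will be re-estimated.

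It can also be said that the restriction may be intended and that depression stayed in the aims by mistake. The documents do not settle this, so the remedy has to allow for either answer. Finally, the hypothesis sentence speaks of mental-health outcomes in general and does not name depression. That is true, but the objective it belongs to lists depression explicitly.

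None of these replies supplies a named depression score or removes the contradiction between the objective and the restriction.

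**Conclusion.** The contradiction stands, in this limited form: depression is a stated aim and a listed outcome of the fourth objective, while the measurement section excludes the one named subscale that would score it and offers no other depression rating. One of four constructs in that objective lacks a depression-specific clinical score at all three measurement times, and the metabolites labelled as depression markers have no such score as a clinical anchor.

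The conclusion assumes that the restriction means what it says and that the General Health Questionnaire is not intended as the depression outcome, since the article assigns it elsewhere. It makes no assumption about whether the depression items are administered.

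The consequence is moderate. The article attaches its primary-outcome label to the first objective, on pulmonary function, and no mental-health measure is in its lists of primary outcomes. The point is worth correcting because the correction is simple and the trial is already recruiting.

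**What to change.** In the section on self-reported measures, replace the restriction with: 'All three DASS-21 subscales (depression, anxiety, stress) will be administered and scored at baseline, week 13 and week 25.' Name the depression subscale as the depression outcome of the fourth objective.

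If the exclusion is deliberate, remove depression from the second aim and the fourth objective instead, and make no depression claim from the metabolomics.

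The first option costs a few more questionnaire items at visits that already take place, with no added visit or blood sample. Patients already enrolled may have incomplete baseline depression data if the items were not given to them. The investigators should establish which items have been administered so far and report the extent of any gap. The second option costs nothing in data collection but gives up a stated objective.
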